### Sample size {14}

In all power calculations, we have assumed a 2:1 allocation ratio (intervention: control) and applied a two-sided significance level of 5%. Our initial assumption was that a total of 219 participants would be available for analysis which, after inflation to allow for 40% attrition gives a total recruitment target of 366 participants (244 intervention and 122 control).

The (primary) power calculation used the power command in Stata 15.1, which yielded 79% power for an effect size of 0.4 standard deviations (0.4SD). While there is no established minimal clinically important difference on the ABI-29 scale, baseline data from male perpetrators in a group support study in the US using the ABI-30 found a standard deviation of 11 giving a detectable effect size corresponding to 4.4 points [60]. Such a difference is considered plausible and of a magnitude worthwhile detecting if the intervention had such an effect.

The design of the intervention allows a rolling intake of participants in the various groups; therefore, there is potential for clustering in that arm (with no such effects in the control arm). The degree of this effect (essentially one of additional inefficiency/compromise on power) will depend on the degree of clustering, the number of intervention groups and the extent to which these groups overlap as men enter and leave them. All of these are difficult to predict; the latter in particular means that a clear definition of a cluster is very likely to be elusive. Hence, we have not allowed for this in the above power calculation but have explored the potential for such clustering effects using the clsampsi command in Stata 15.1 [61]. Notwithstanding these uncertainties, with a (conservative) intra-cluster correlation coefficient (ICC) of 0.05, the above sample size would yield a power of 80% to detect a 0.435SD effect size. The originally planned sample size would therefore have about 80% power to estimate an effect size of between 0.4 to 0.435 SD, covering situations with zero/negligible clustering and for a conservative ICC.

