### Reduction in sample size

Due to difficulties experienced in meeting the original target for recruitment, primarily from the first 18 months of recruitment being conducted during the COVID-19 pandemic, along with an extended recruitment period, a reduction of 50 in this target was subsequently approved by the Programme Steering Committee (PSC), Data Monitoring and Ethics Committee (DMEC), and the funding body. Using the SD of 10.7 derived from 201 baseline measurements in this trial and again assuming 40% attrition, the revised sample size of 316 to be recruited provides approximately 80% power to detect an effect size of 0.43SD under the primary assumption of no clustering. This slightly revised target difference, corresponding to 4.6 ABI-29 scale points (compared with the original of 4.4), was still deemed plausible and worth detecting to drive implementation of the programme after the trial.

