### Plans to promote retention and complete follow-ups {18b}

The research team will endeavour to maintain contact and trial engagement with all participants every 6–8 weeks via text messaging (according to contact preference). Two to three weeks prior to a questionnaire’s due date, participants will be alerted by the method of their choice (text, email, or phone call) to the forthcoming questionnaire. Up to seven reminders may be sent via different means (calls, text, email) if the follow-up questionnaire has not been completed.

An eligible potential participant who chooses not to participate is counted as a *decline* and reasons for declining will be collected. Once consented, a participant may withdraw at any time should they wish. Participants allocated to the intervention who no longer wish to be involved in the programme will still be followed up with questionnaires. No further follow-up data will be requested from any individuals who explicitly wish to fully withdraw from the trial, but data collected up to that point will be retained and included for data analysis.

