## Statistical methods

### Statistical methods for primary and secondary outcomes {20a}

Descriptive statistics will be used to summarise all baseline characteristics and outcome measures in both study arms.

The primary outcome of the ABI-29 will be analysed using a linear regression model that will include the baseline ABI-29 score, the stratification factor of centre and minimisation factor of relationship status. The primary analysis will be performed on a complete case basis and according to the arm to which the participant was allocated. Sensitivity analyses will be conducted to explore the effects of the number of sessions attended and (if possible, given the eventual structure of the intervention groups) any effects of clustering. Secondary outcomes will be analysed using linear or logistic regression models as appropriate. If found, substantial imbalances of variables at baseline (determined using descriptive statistics) will be explored in sensitivity analyses.

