### Methods for additional analyses (e.g. subgroup analyses) {20b}

Further secondary analyses will include pre-specified subgroup analyses according to age and to the two stratification/minimisation variables, investigated by introducing the relevant interaction with treatment allocation into the regression model. In addition, to assess the stability of any intervention effect, we will fit a mixed model for the primary outcome(s) at 4, 8 and 12 months, adjusted for baseline measures. We will also investigate obtaining complier-average causal effect (CACE) estimates using instrumental variable techniques to investigate the efficacy of the intervention while accounting for degree of adherence to the programme [64].

A statistical analysis plan will be produced by the trial team and agreed with the PSC and DMEC before the commencement of any comparative analyses. It will be posted on PURE, UoB’s research information system and repository of scholarly works: http://www.bristol.ac.uk/red/research-policy/pure/.

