### Methods in analysis to handle protocol non-adherence and any statistical methods to handle missing data {20c}

Intention-to-treat analysis will be carried out. All randomised participants, including those who drop out of or are excluded from the intervention will be included in the analysis. Sensitivity analyses will be conducted to explore the effects of missing data.

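### The complete-case primary analysis does not fit the statement that all randomised men are included; with 40% attrition planned, the mixed model already in the plan is the better primary analysis

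*Protocol article*

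**What the plan says.** The primary outcome is men's self-reported ABI-29 at 12 months (Abstract, Methods). *Statistical methods for primary and secondary outcomes {20a}* specifies a linear regression on baseline ABI-29, centre and relationship status, and sets the analysis population: "The primary analysis will be performed on a complete case basis and according to the arm to which the participant was allocated".

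*Methods in analysis to handle protocol non-adherence and any statistical methods to handle missing data {20c}* announces an intention-to-treat analysis and continues: "All randomised participants, including those who drop out of or are excluded from the intervention will be included in the analysis". It promises sensitivity analyses for missing data without naming a method.

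*Reduction in sample size* sets the scale of the expected loss: "Using the SD of 10.7 derived from 201 baseline measurements in this trial and again assuming 40% attrition", with 316 men to be recruited.

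*Methods for additional analyses {20b}* already contains a longitudinal analysis: "we will fit a mixed model for the primary outcome(s) at 4, 8 and 12 months, adjusted for baseline measures". Its stated purpose is to assess how stable any effect is, so it ranks as secondary.

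**The concern.** A man without a 12-month ABI-29 score cannot enter a complete-case regression of that score. Under the planned attrition, two in five randomised men would be absent from the analysis that carries the trial's conclusion, while {20c} tells the reader that all randomised men are in it.

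The choice also matters statistically. Complete-case regression is unbiased if, given arm, baseline ABI-29, centre and relationship status, being missing at 12 months is unrelated to the 12-month score. It ignores what the 4- and 8-month questionnaires show about men who are lost later. If men with worse interim scores are lost more readily in one arm than in the other, the completers in the two arms are no longer comparable. The resulting error can look like benefit or hide it. The planned mixed model uses those interim scores.

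**Working it through.** **Step 1. Reproduce the plan's power.** Inputs from *Sample size {14}* and *Reduction in sample size*: two-sided 5%, 2:1 allocation, 40% attrition. With n analysable men split 2:1, power is approximately Φ(d·√(2n/9) − 1.96), where d is the effect in SD units.

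- Original: "a total of 219 participants would be available for analysis", d = 0.4. √(2·219/9) = 6.98, and 0.4 × 6.98 − 1.96 = 0.83, giving 79.7% (79.3% with the noncentral t). Stated: 79%. Recruitment: 219/0.6 = 365. Stated: 366 (244 + 122).
- Revised: 316 × 0.6 = 189.6, d = 0.43. √(2·189.6/9) = 6.49, and 0.43 × 6.49 − 1.96 = 0.83, giving 79.7% (79.2% with t). Stated: about 80%. Target: 0.43 × 10.7 = 4.6 points, as stated.

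The power figures reproduce and already refer to completers.

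**Step 2. Count the men left out.** 316 × 0.40 = 126.4, so about 126 men are outside a complete-case analysis at 12 months.

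**Step 3. Bias.** A simulation (2,000 replicates per scenario) compared complete-case regression at 12 months, adjusted for baseline, with the maximum-likelihood repeated-measures estimate at 12 months.

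- From the protocol: 316 men, 2:1, SD 10.7, true benefit 0.43 SD, 40% lost by month 12.
- Assumed: equal correlation of 0.5 or 0.7 between all visits; the benefit the same at each visit; men do not return once lost; losses over months 4/8/12 split 50/25/25% (early) or 20/30/50% (late); overall loss equal in both arms; log-odds of dropout 0 or ±0.7 per SD of the last observed score. Centre and relationship status were left out.

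Bias of the complete-case estimate in ABI-29 points (negative means benefit is overstated; Monte Carlo error about 0.03):

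| Dropout and last score | 0.5, early | 0.5, late | 0.7, early | 0.7, late |
|---|---|---|---|---|
| Unrelated | −0.02 | −0.04 | 0.04 | 0.02 |
| Same in both arms | −0.02 | 0.00 | 0.03 | 0.02 |
| Higher scorers lost, intervention arm only | −0.45 | −0.69 | −0.38 | −0.55 |
| Opposite directions by arm | −0.95 | −1.37 | −0.83 | −1.18 |

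Against 4.6 points, the third row is 0.38/4.6 = 8% to 0.69/4.6 = 15%, and the fourth is 0.83/4.6 = 18% to 1.37/4.6 = 30%. The standard error was about 1.4 to 1.5 (correlation 0.5) or 1.2 (correlation 0.7), so these biases are roughly 0.3 to 0.5 and 0.65 to 1.0 standard errors. The repeated-measures estimate stayed within about 0.04 points throughout. By symmetry, reversing the direction of dropout reverses the sign.

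**Step 4. Precision.** The ratio of complete-case to repeated-measures variance was 1.02 to 1.08. In the formula of Step 1, about 190 analysable men become about 194 to 205, and power moves from 79.7% to about 80.5% to 83%. With no attrition, 316 men would give 95.0%, so the mixed model recovers only 1 to 3 of the 15 points lost.

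**Step 5. Limits of the mixed model.** Men with no follow-up score add nothing to a model adjusted for baseline. Under the assumed timings that is 126.4 × 0.2 = 25 to 126.4 × 0.5 = 63 men. The model also relies on missingness being explained by observed scores. If the gap between missing and observed men differs between arms by 0.25 SD beyond that, the bias is about 0.40 × 0.25 × 10.7 = 1.1 points.

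**The case against.** The best defence is that {20c} is about adherence. It singles out men who leave or are removed from the programme, and {20a} agrees by analysing men as allocated. On that reading the two sections mean the same thing. This has force as an account of intent, but the subject of the sentence is all randomised participants, under a heading that also covers missing data. A complete-case analysis cannot deliver that at 40% attrition, so the wording conflict stands.

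The second defence is that the bias is hypothetical. The document does not show that loss to follow-up differs by arm in its relation to abuse; the correlations, slopes and timing are assumed; and the simulated dropout depends on observed scores, which is the condition under which the mixed model does well. All of this stands and limits how much weight the sizes can bear. It does not favour complete-case regression, which gave no smaller bias in any pattern beyond simulation error and was slightly less precise in all of them.

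The third is that much is already planned: missing-data sensitivity analyses, the longitudinal model, and an analysis plan to be agreed before any comparative analysis. That is right. Imputation models, auxiliary variables and similar detail belong in that plan, and their absence here is no fault. What remains is a stated choice of primary analysis and a stated population that do not match.

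**Conclusion.** The point holds as a should-fix. {20a} and {20c} cannot both be met as worded, and about 126 of 316 men would be outside the primary analysis. The bias is conditional. It is 0.4 to 0.7 points if loss depends on earlier scores in the intervention arm only, 0.8 to 1.4 points if it runs in opposite directions, and close to zero if loss is random or equally score-related in both arms. These sizes rest on the assumptions in the working. The precision gain is minor, so possible bias is the main reason to change.

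A reader might infer more than the document supports:

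- *That leaving the programme creates the arm difference, since only intervention men can leave it.* {11b} and {18b} keep these men in follow-up unless they withdraw fully. Exclusion from the trial because of risk is not confined to one arm. The relevant loss is loss to follow-up.
- *That {18b} also contradicts {20a}.* It says of men who withdraw that "data collected up to that point will be retained and included for data analysis", but does not say the primary analysis. The planned mixed model can use those scores.
- *That the sample size is wrong.* It was calculated on completers and reproduces.
- *That the mixed model settles everything.* It omits men with no follow-up score and does not protect against loss that depends on unobserved abuse.

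**What to change.** 1. Take the primary 12-month treatment contrast from the mixed model already planned in {20b}: ABI-29 at 4, 8 and 12 months, with visit-by-arm terms, baseline ABI-29, centre and relationship status, and every man with at least one follow-up score included. The visit-by-arm terms are needed so that the result is the 12-month effect and not an average over visits.
2. Keep the complete-case regression of {20a} as a sensitivity analysis.
3. Reword {20c} to say that men are analysed as allocated whatever their attendance, and to state which men contribute to the primary analysis. Changing the model alone does not make the present sentence true.
4. Include a missing-not-at-random analysis among the sensitivity analyses that {20c} already promises, with its details left to the statistical analysis plan.

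The cost is wording in the protocol and analysis plan, to be settled before any comparative analysis. No new data are needed and the sample size does not change. The downside is a slightly more complex primary model.

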### Interim analyses {21b}

Not applicable unless requested by the DMEC.

### Methods for additional analyses (e.g. subgroup analyses) {20b}

Further secondary analyses will include pre-specified subgroup analyses according to age and to the two stratification/minimisation variables, investigated by introducing the relevant interaction with treatment allocation into the regression model. In addition, to assess the stability of any intervention effect, we will fit a mixed model for the primary outcome(s) at 4, 8 and 12 months, adjusted for baseline measures. We will also investigate obtaining complier-average causal effect (CACE) estimates using instrumental variable techniques to investigate the efficacy of the intervention while accounting for degree of adherence to the programme [64].

A statistical analysis plan will be produced by the trial team and agreed with the PSC and DMEC before the commencement of any comparative analyses. It will be posted on PURE, UoB’s research information system and repository of scholarly works: http://www.bristol.ac.uk/red/research-policy/pure/.

### Methods in analysis to handle protocol non-adherence and any statistical methods to handle missing data {20c}

Intention-to-treat analysis will be carried out. All randomised participants, including those who drop out of or are excluded from the intervention will be included in the analysis. Sensitivity analyses will be conducted to explore the effects of missing data.

#### Economic evaluation

The economic evaluation over a 1-year time horizon will be conducted from three perspectives: health and social care, public sector and society will employ a cost-consequences framework such that costs are reported alongside the economic outcomes (QALYs (derived from the SF-12 [38], EQ-5D-5L [37] and CHU-9D [40]) and ICECAP-A [39] as well as the primary and other secondary outcomes.

The resource use will be valued using the most up to date reference costs where possible; otherwise, estimates from literature and those reported by participants will be used, and if necessary, adjusted for inflation [65, 66].

Resource use and costs will be grouped by the categories: health and social care, public sector, participants, society. Within these categories, the resource use, and costs to the men, supporting (ex) partners and children will be reported separately.

Descriptive statistics will be used to summarise resource use, costs and outcome measures by study arm.

Appropriate regression analysis will be used to analyse the costs and outcomes. Costs will be adjusted for the baseline ABI-29 score, the stratification factor of centre and minimisation factor of relationship status, additionally the QALYs will be adjusted for the baseline utility score [67].

Sensitivity analyses will be used to explore the effects of methodological assumptions as well as those of missing data.

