#### Secondary outcomes: Police data

We will collect police-recorded DVA incidents and crimes perpetrated by our male participants. We will collect data for the 12-month period prior to randomisation and 12 months post-randomisation (see Supplementary Information: RESPONSE TO COVID-19 PANDEMIC). We will request for each male participant the following: (a) a count of the number of police incidents/crimes flagged as DVA; (b) the date(s) of the incident(s)/crimes; (c) the police case outcome for each incident/crime (for example, *No Further Action*, *Charge*, *Domestic Incident only*); (d) a count of the number of entries on the Log of Enquiries for each of these incidents; (e) risk scores/ratings for each of these incidents where available and whether referred to Multi Agency Risk Assessment Conference (MARAC).

Pre- and post-randomisation police DVA incident data are another measure of participant behaviour change. The risk scores/ratings and the police case outcome will also give an indication of the severity and nature of the abuse. Finally, the police data give an external source of data distinct from the participants’ self-reports of abuse.

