#### Economic evaluation measures

All resource use in relation to participants’ own use of health services (secondary, community and mental health based), medications, personal social services (e.g. drug and alcohol team), voluntary sector services, criminal justice and legal services will be collected for the 12 months following randomisation by means of self-reported questionnaire, and in the case of police incidents, the police-recorded data. These questionnaires will also collect information on out-of-pocket expenses, e.g. personal counselling, complementary therapy, relocation costs and childcare costs, in addition to time off work.

Additionally, the use of health services and time off school by any children who primarily live with the supporting (ex)partner is being collected through their respective questionnaire. Three outcomes for the economic evaluation: EQ-5D-5L [38], SF-12 [39] and ICECAP-A [40] are being collected for all participants; additionally, the proxy version of the CHU-9D [56] is being collected in the supporting (ex)partner questionnaire for the child whose birthday is first in the calendar year. The NICE recommended mapping function [57] will be used to calculate quality-adjusted life years (QALYs) in relation to the EQ-5D-5L. The SF-6D and its preference weights [58] will be used to calculate QALYs in relation to the SF-12. A published value set [59] will be used to calculate QALYs in relation to the CHU-9D.

The resource use and costs incurred in relation to the intervention: the group intervention (both main and RPG) as well as the individual sessions for men and support from the WSW for the (ex)partners will be obtained from the budget breakdown.

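### Cost regressions leave out the police record for the year before randomisation, a planned baseline value that would cheaply sharpen men's public-sector and societal cost differences

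*Protocol article*

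**What the plan says.** The Economic evaluation section of the statistical methods names three covariates for the cost analysis: "Costs will be adjusted for the baseline ABI-29 score, the stratification factor of centre and minimisation factor of relationship status". The same sentence treats QALYs differently: "additionally the QALYs will be adjusted for the baseline utility score". No baseline counterpart is named for costs. The evaluation "will be conducted from three perspectives: health and social care, public sector and society", and within the cost categories the men's costs are reported apart from those of (ex)partners and children.

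The section Secondary outcomes: Police data plans an equal window on each side of randomisation: "We will collect data for the 12-month period prior to randomisation and 12 months post-randomisation". The request is made man by man: "We will request for each male participant the following". Under Economic evaluation measures, resource use after randomisation comes from questionnaires and, "in the case of police incidents, the police-recorded data".

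The economic section closes with a general provision: "Sensitivity analyses will be used to explore the effects of methodological assumptions as well as those of missing data". It names no covariate.

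**The concern.** One source, with windows of equal length, is planned to supply both a component of the men's cost and that component's baseline value. The covariate list uses only self-reported abuse and the two allocation factors. Baseline ABI-29 does not replace the police record: the police data section itself presents police data as external information separate from what participants report. Trial design {8} and Sequence generation {16a} balance only centre and relationship status, so nothing in the design balances prior police contact.

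At stake is the precision of the men's cost difference in two of the three perspectives (public sector and society), and its exposure to a chance difference between arms in prior police contact. Health and social care cost is little affected. The point does not depend on whether the resource-use questionnaire is completed at baseline.

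**Working it through.** **Sample size for the illustration.** The documents give no precision figure for costs, so the only stated figure to reproduce is the revised power for the primary outcome (Reduction in sample size): 316 recruited, 40% attrition, 2:1, 0.43 SD, about 80% power.

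- Analysed: 316 × 0.6 = 189.6, about 190, or 126.7 and 63.3 by arm.
- SE of a standardised difference: √(1/126.7 + 1/63.3) = 0.154.
- Power at two-sided 5%: Φ(0.43/0.154 − 1.96) = 79.8% by normal approximation (79.4% by t-test). This agrees with the stated figure.

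I use 190 below. The 40% is the protocol's attrition assumption for the ABI-29; the number with police data could differ.

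**Gain for the police-cost component.** Adding a baseline covariate with partial correlation r, given ABI-29, centre and relationship status, multiplies the variance of the arm difference by 1 − r². The documents do not give r; 0.3 to 0.5 is an assumption.

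- r = 0.3: variance × 0.91, SE × √0.91 = 0.954, a fall of 4.6%.
- r = 0.5: variance × 0.75, SE × √0.75 = 0.866, a fall of 13.4%.

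**Gain for men's total public-sector cost.** Let f be the share of that cost's variance due to police cost, also not given. If the prior count predicts only the police part, and the other parts are uncorrelated with it, the variance factor is 1 − f·r².

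| f | r | Variance factor | SE factor | Fall in SE | 190 men are worth |
|---|---|---|---|---|---|
| 0.25 | 0.3 | 0.978 | 0.989 | 1.1% | 194 |
| 0.25 | 0.5 | 0.938 | 0.968 | 3.2% | 203 |
| 0.5 | 0.3 | 0.955 | 0.977 | 2.3% | 199 |
| 0.5 | 0.5 | 0.875 | 0.935 | 6.5% | 217 |

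Over a wider range, the fall runs from 0.1% (f = 0.25, r = 0.1) to about 13% (f = 0.5, r = 0.7).

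**Chance imbalance.** The 95% range for a standardised baseline difference is ±1.96 × 0.154 = ±0.30 SD with 190 men. With all 316 (about 211 and 105) it is ±1.96 × √(1/211 + 1/105) = ±0.23 SD. An imbalance of d shifts the unadjusted police-cost difference by about r·d. With d = 0.30, that is 0.09 SD at r = 0.3 and 0.15 SD at r = 0.5. The latter is about one standard error (0.154) and lies at the edge of what chance would produce.

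**The case against.** The strongest reply is that nothing in the section is wrong. The covariate set is coherent, randomisation keeps the cost contrast unbiased, and one more prognostic covariate is a matter of choice. That stands as to validity: the point is about efficiency and chance imbalance only.

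Several stronger readings are tempting, and the documents do not support them:

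- *The QALY and cost models contradict each other.* They do not. If QALYs are calculated as an area under the curve, baseline utility is part of the outcome; cost before randomisation is not part of 12-month cost.
- *Prior police contact is an established predictor of cost.* No passage shows this. Table 1 excludes court-mandated men, men judged too high risk and men under current criminal justice investigation, which may narrow the spread of prior contact and lower r.
- *The value will exist for every man.* The plan is to request it for each man; completeness is not reported, and Table 1 names four police forces.
- *The 5% to 13% applies to total cost.* It applies to the police part. Men's costs also include health care, medication, social and voluntary services, legal services, out-of-pocket spending and time off work.

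It can also be said that the full protocol or the analysis plan, neither shown, may hold a longer list. That is possible, but the article does not leave the list open: it states one, and following it would omit the police term. The general sensitivity analyses do not fill the gap because they name no covariate. The provision in section {20a} to explore substantial baseline imbalances depends on the observed data and is not stated for costs.

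**Conclusion.** The point holds as a minor, low-cost improvement to a stated covariate list. The plan contains no error, contradiction or bias here.

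Under an assumed partial correlation of 0.3 to 0.5, the standard error falls by about 5% to 13% for the police-cost component. For men's total public-sector cost it falls by about 1% to 6.5% if police cost is a quarter to a half of the variance. Neither the correlation nor the share is in the documents, so these figures show a plausible scale and are not estimates for this trial. For societal cost the police share is not given either; the gain would be smaller wherever that share is smaller. The protection against chance imbalance is the same benefit seen in a single realised allocation.

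**What to change.** Add to the Economic evaluation section, and carry into the analysis plan before any comparative analysis: *Men's public-sector and societal costs will also be adjusted for the number (or cost) of police-recorded DVA incidents in the 12 months before randomisation.*

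Keep the covariate out of the models for the separately reported costs of (ex)partners and children. State in advance how a missing count is handled so that no man is dropped from the analysis, and allow a categorised or transformed count if the distribution is skewed, so that a few large values do not dominate the fit.

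The cost is one sentence and one more model term (a few if the count is categorised). The data are already to be requested, so no new collection is needed. The downside is small: missing or skewed counts need the handling just described.
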